### Sample Size and Power Calculation

If we recruit a total of 400 LKDs over a 2-year period and the proportion of control arm LKDs with compliant follow-up is 50%, we will have 80% power to detect a difference of 13.8% and 90% power to detect a difference of 15.9% (Table 1). If the projected follow-up rate of donors in the intervention arm is 67% (the minimum threshold for policy compliance), this study will have 79% power to detect a difference. If the follow-up rate in the intervention arm is 70%, this study will have 95% power to detect a difference (Figure 3). There is a possibility that we might face low levels of recruitment or high levels of dropout. If we are only able to recruit 300 LKDs over 2 years, then we will have 80% power to detect a difference of 15.9% and 90% power to detect a difference of 18.3%. If we are only able to recruit 200 LKDs over 2 years, we will have 80% power to detect a difference of 19.3% and 90% power to detect a difference of 22.1%.

**Table 1 table1:** Power size calculations.

Number of recruited live kidney donors	Control proportion	Intervention proportion (80% power)	Delta (80% power)	Intervention proportion (90% power)	Delta (90% power)
200	0.50	0.693	0.193	0.721	0.221
300	0.50	0.659	0.159	0.683	0.183
400	0.50	0.638	0.138	0.659	0.159

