### Current Landscape of Living Kidney Donor Follow-Up

OPTN/UNOS has collected postdonation follow-up data on LKDs since 1999. However, LKD follow-up has remained consistently poor. This prompted a national policy that began requiring centers to collect these data beginning in 2013 [10,11]. OPTN/UNOS now requires transplant hospitals to collect and submit clinical data (the presence of HTN, diabetes, dialysis, kidney-related complications, recent hospitalizations, medical insurance status, income, and vital status) for 80% and laboratory data (serum creatinine and urine protein) for 70% of LKDs for 2 years postdonation (Multimedia Appendix 1). Transplant hospitals are required to collect these data from each LKD within a 120-day period (60 days before or after the 6-month, 1-year, or 2-year postdonation date) for each follow-up visit [10]. Implementation of this requirement has shown limited improvement. In a national study, we found that only 43% (87/202) of transplant hospitals met OPTN/UNOS-mandated 6-month, 1-year, and 2-year thresholds for LKDs who donated in 2013 [12]. In the face of barriers, such as cost, LKD inconvenience, and the burden of data collection [13,14], transplant hospitals lack the tools to improve LKD engagement.

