**Figure 2 figure2:**
[figure not shown]
Schematic of the study design. LKD: living kidney donor.

We will assign participants either to the intervention (mKidney system) or the control arm (standard of care) using block randomization with block sizes ranging from 2 to 8. Block randomization will improve the probability of balanced groups over the course of the study. A statistician on the Johns Hopkins study team, blind to group allocations, will use this method to generate a list of sequential group assignments using Stata 15 for Linux (StataCorp Inc). The list will be used to create sequentially numbered, sealed envelopes that will be used to allocate consenting participants to the control or intervention arms of our study. Each patient will have a 50% chance of being assigned to the intervention arm of the study. Patients, health care workers on the study team, and study team members responsible for data collection and analysis will be aware of which arm participants are randomized to. Therefore, this study will not be blinded to providers, patients, or study personnel.

Study personnel will assist participants assigned to the mHealth intervention arm with downloading the mKidney app and explain its functioning. After enrollment in the study, participants in the intervention arm will receive notifications and have the ability to complete a questionnaire documenting their remote standard-of-care visit and enter the required laboratory values at 6 months, 1 year, and 2 years postdonation using the mKidney app. Participants in the control arm will be instructed to complete the required follow-up as is standard of care but will not use the mKidney app to do so (Figure 2).

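### The power section labels 67% as the policy minimum, which conflicts with the protocol's own 80% and 70% limits and cannot be derived from them; the powers given at 67% and 70% are also wrong

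*Protocol article*

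**What the plan says.** In Methods, Sample Size and Power Calculation, the planning case is set by "If we recruit a total of 400 LKDs over a 2-year period" and by a control rate given as "the proportion of control arm LKDs with compliant follow-up is 50" per cent. The text then takes an intervention-arm rate of "67% (the minimum threshold for policy compliance" and concludes that "this study will have 79% power to detect a difference". It adds a second scenario: "If the follow-up rate in the intervention arm is 70%, this study will have 95% power to detect a difference". For 400 donors, Table 1 gives detectable intervention rates of 0.638 (80% power) and 0.659 (90% power).

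The Introduction, under Current Landscape of Living Kidney Donor Follow-Up, describes the policy differently. Hospitals must submit clinical items, ending with "medical insurance status, income, and vital status) for 80% and laboratory data (serum creatinine and urine protein) for 70% of LKDs". These are two separate limits, and they apply to the transplant hospital.

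Methods, Study Procedure, defines the primary outcome per donor and jointly: every required component, within the time window, at the three visits. Hospital-level compliance with the reporting requirements is a separate secondary outcome, assessed at each visit.

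**The concern.** The 67% label is a factual statement about the policy, and the protocol's only account of that policy contradicts it. It is also the only rationale offered for either power scenario in the text, so a reader will take it as the rate at which the intervention achieves compliance.

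Three things are at stake. The secondary outcome is compliance with this same policy, so the protocol should not give the limit in two incompatible ways. The pilot is meant to inform the design of a larger trial, and a wrong benchmark or a wrong power could carry over into it. Finally, the 79% attached to 67% conflicts with the table in the same section, so a reader cannot tell which power figures to rely on.

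**Working it through.** **Inputs.** Total 400 donors, control rate 50%, intervention rates 67% and 70%, stated powers 79% and 95% (all from Sample Size and Power Calculation). Allocation is 1:1 ("Each patient will have a 50% chance of being assigned to the intervention arm of the study", Study Procedure), so n = 200 per arm. Policy limits are 80% clinical and 70% laboratory (Introduction). The significance level is not stated; two-sided 5% is assumed and tested in step 1.

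**Formula.** With p̄ = (p1 + p2)/2 and z = 1.96,

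power = Φ{ [(p2 − p1) − z·√(2p̄(1 − p̄)/n)] / √([p1(1 − p1) + p2(1 − p2)]/n) }.

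**Step 1: reproduce Table 1.** Solving for p2 with p1 = 0.50 gives, for 80% and 90% power:
- 200 donors: 0.693 and 0.721
- 300 donors: 0.659 and 0.683
- 400 donors: 0.638 and 0.659

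All six entries match to three decimals, which supports the two-sided 5% assumption.

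**Step 2: power at 67%, n = 200 per arm.** p̄ = 0.585.
- Null term: 1.96 × √(2 × 0.585 × 0.415/200) = 1.96 × 0.04927 = 0.0966.
- Denominator: √((0.25 + 0.2211)/200) = 0.04853.
- z-value: (0.17 − 0.0966)/0.04853 = 1.51, so power = 93.5%. Stated: 79%.

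**Step 3: power at 70%.** p̄ = 0.60.
- Null term: 1.96 × √(0.48/200) = 0.0960.
- Denominator: √((0.25 + 0.21)/200) = 0.04796.
- z-value: (0.20 − 0.0960)/0.04796 = 2.17, so power = 98.5%. Stated: 95%.

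**Step 4: sensitivity.** Across two-sided 5% variants (continuity correction, arcsine, unpooled variance), power is 92.1% to 93.9% at 67% and 98.1% to 98.7% at 70%. A one-sided 5% test gives 96.7% and 99.4%. A two-sided 1% test gives 81.3% and 93.8%. None of these returns the stated pair. A power of 79% at 67% would correspond to 128 donors per arm, and 95% at 70% to 153 per arm, so one smaller sample does not explain both. Table 1 alone settles the first figure: if power is already 90% at 65.9%, it cannot be 79% at 67%.

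**Step 5: can 67% be derived from 80% and 70%?** Let C and L be the shares of donors with complete clinical and laboratory data, and J the share with both. Then max(0, C + L − 1) ≤ J ≤ min(C, L). With C = 0.80 and L = 0.70:
- lowest J: 0.80 + 0.70 − 1 = 0.50
- highest J: 0.70
- J if the two were independent: 0.80 × 0.70 = 0.56

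So 67% is neither end of the range nor the independence value.

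**Step 6: what does a joint rate of 67% imply about compliance?** Two possible arms:
- 67% both, 13% clinical only, 3% laboratory only, 17% neither: C = 67 + 13 = 80% and L = 67 + 3 = 70%. Both limits are met.
- 67% both, 33% neither: C = L = 67%. Both limits are missed.

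The joint rate alone does not decide compliance.

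**The case against.** The strongest reply is that little depends on the label. No analysis rule or success criterion uses 67%. The arms are compared by regression, and hospital compliance is a separate outcome tied to the reporting requirements themselves. Enrolment of 400 does not rest on 67%, and Table 1 works from the 50% control rate alone. The study is also described as an exploratory pilot. All of this stands, and it limits the consequence to a wrong statement and two wrong powers.

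A reader might infer something stronger: that an arm at 67% would necessarily fail both limits, since 67% of 200 is 134 donors, against 140 for the 70% limit and 160 for the 80% limit. The documents do not support that. The 67% is set against a control rate of compliant follow-up and belongs to a joint outcome, whereas 70% and 80% are limits for single components. Each component rate is at least as high as the joint rate, and the first arm in step 6 of the working meets both limits. If the rate is read as completion at all three visits, the rates at each single visit are at least as high again. The shortfalls of 6 and 26 donors compare unlike quantities.

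What the reply does not remove is that the label contradicts the Introduction and that the 79% contradicts Table 1.

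**Conclusion.** The point holds as an error of labelling and of arithmetic in one short stretch of the power section. The figure of 67% is not a policy threshold anywhere in the document, and it cannot be obtained from the 80% and 70% limits for a joint outcome, where the range is 50% to 70% when both limits are just met. An arm at 67% may pass or fail either limit. It would be wrong to call such an arm compliant on that figure alone, and equally wrong to call it non-compliant.

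The stated powers are too low by about 14 percentage points at 67% (93.5% against 79%) and about 3 at 70% (98.5% against 95%). These values assume a two-sided 5% level, 200 donors per arm and a 50% control rate. The errors understate power, so they do not suggest that the trial is too small. Sample size, outcome definitions and the planned comparison are unaffected.

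**What to change.** In Sample Size and Power Calculation:
- Remove the description of 67% as a policy threshold. Keep 67% and 70% only as planning scenarios for the joint outcome.
- Restate the powers for 400 donors against a 50% control rate as about 93% at 67% and about 98% at 70%, and state the significance level and sidedness.
- State that hospital-level compliance is judged separately for clinical and laboratory data against the 80% and 70% given in the Introduction. If the sponsor has a source for 67%, cite it and reconcile the two sections.

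Do not add power figures for laboratory or clinical data alone unless control rates for those components are given: the 50% is a rate of overall compliant follow-up and cannot be paired with component targets. Figure 3 is not available here; amend it only if it marks 67% or shows the uncorrected powers.

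The cost is a few sentences of text, with no change to design, enrolment or analysis.

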### Study Population

We plan to enroll 400 LKDs who have donated a kidney at Methodist Specialty and Transplant Hospital in San Antonio, Texas, during the study period. LKDs randomized to the intervention arm (approximate n=200) will receive the mKidney system, whereas LKDs randomized to the control arm (approximate n=200) will receive the current standard of follow-up care.

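### With 400 donors, 79% power at a 67% follow-up rate contradicts Table 1 (90% power at 65.9%), and 95% at 70% does not follow from the same inputs

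*Protocol article*

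**What the plan says.** The power paragraph opens by fixing its inputs: "If we recruit a total of 400 LKDs over a 2-year period and the proportion of control arm LKDs with compliant follow-up is 50" percent. On that basis, "we will have 80% power to detect a difference of 13.8% and 90% power to detect a difference of 15.9" percent. Table 1 repeats the two results in its 400-donor row as intervention proportions of 0.638 and 0.659.

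Two further scenarios follow at once. The first is an intervention rate of 67%, given as "the minimum threshold for policy compliance), this study will have 79% power to detect a difference". The second reads: "If the follow-up rate in the intervention arm is 70%, this study will have 95% power to detect a difference", with a reference to Figure 3. Only after these does the paragraph turn to 300 and then 200 donors.

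Allocation is equal. Study Procedure states: "Each patient will have a 50% chance of being assigned to the intervention arm of the study". Study Population plans about 200 donors per arm. The paragraph and Table 1 give no alpha or sidedness.

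**The concern.** At a fixed sample size, control rate and alpha, power rises with the difference. The paragraph gives 90% power at 15.9 points and then 79% at 17 points, so one of the two must be wrong. This can be seen without any calculation and holds whatever alpha was used.

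The 95% at 70% is not out of order in the same way, since it lies above 90% at a higher rate. However, the two 400-donor entries in Table 1 fix the rest of the power curve, and 95% belongs to a rate well below 70%.

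The 67% scenario is the one the article ties to policy compliance. Read from Table 1, power there exceeds 90%. Read from the sentence, it falls short of 80%. The type II error is either about 6.5% or 21%, roughly a threefold difference. The same paragraph is used to judge how much low recruitment or dropout the trial can bear, and the wrong figure makes 400 donors look marginal at that target.

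**Working it through.** **Inputs**

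- Total 400 and control rate 50%: Sample Size and Power Calculation.
- Equal allocation, n = 200 per arm: Study Population and Study Procedure.
- Two-sided alpha 0.05: an assumption, adopted because it reproduces every cell of Table 1.

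**Formula** (two proportions, normal approximation, pooled variance under the null)

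Power = Φ[(p2 − p1 − 1.96·SE0) / SE1], where SE0 = √[2·p̄(1 − p̄)/n], SE1 = √{[p1(1 − p1) + p2(1 − p2)]/n} and p̄ = (p1 + p2)/2.

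**Step 1: reproduce Table 1.** Solving for p2 gives:

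| Total | 80% power: computed | 80% power: Table 1 | 90% power: computed | 90% power: Table 1 |
|---|---|---|---|---|
| 200 | 0.6932 | 0.693 | 0.7212 | 0.721 |
| 300 | 0.6591 | 0.659 | 0.6827 | 0.683 |
| 400 | 0.6383 | 0.638 | 0.6592 | 0.659 |

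All six cells agree, so the formula and the inferred alpha are those behind the table.

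**Step 2: apply the same formula to the two disputed scenarios.**

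- 67%: p̄ = 0.585, SE0 = 0.0493, SE1 = 0.0485. (0.17 − 1.96 × 0.0493)/0.0485 ≈ 1.51, so power is 93.5%. Stated: 79%, a gap of 14.5 points.
- 70%: p̄ = 0.600, SE0 = 0.0490, SE1 = 0.0480. (0.20 − 1.96 × 0.0490)/0.0480 ≈ 2.17, so power is 98.5%. Stated: 95%, a gap of 3.5 points.

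In reverse, with 400 donors and control 50%, 79% power belongs to an intervention rate of 63.7% and 95% to 67.6%.

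**Step 3: vary the test.**

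| Method | 67% | 70% |
|---|---|---|
| Pooled variance | 93.5% | 98.5% |
| Continuity correction | 92.1% | 98.0% |
| Unpooled variance | 93.9% | 98.6% |
| Arcsine | 93.4% | 98.4% |
| Fisher exact | 91.9% | 98.0% |

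The choice of test explains neither stated figure.

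**Step 4: look for inputs that would give both 79% and 95%.**

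- *Sample size, control 50%:* 79% at 67% needs about 256 donors in total, and 95% at 70% needs about 306. With 300 donors, power is 94.6% at 70% but 85.2% at 67%.
- *One-sided 0.05 with 200 donors:* 79.0% at 67%, but 89.8% at 70%.
- *Control rate, 400 donors:* 79% at 67% needs 53.5%, where 70% gives 92.7%. In the other direction, 95% at 70% needs 52.6%, where 67% gives 84.0%. A control rate of 53.2% comes close to both, with 80.7% and 93.5%.
- *Alpha, 400 donors, control 50%:* 79% at 67% needs a two-sided alpha of about 0.008. Power is then about 92.7% at 70% and about 55% at 63.8%, which no longer fits Table 1.
- *Sample size and control rate together:* both figures are met with about 334 donors per arm and a control rate of 56.6%. The article states neither value.

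**The case against.** The best defence is that 79% and 95% come from Figure 3, which could not be seen, and that the figure may rest on another control rate. At 53.2%, the computed 80.7% and 93.5% are each within 2 points of the stated pair. That is a plausible origin and it cannot be ruled out, so the cause of the error remains unknown. It does not rescue the text. The paragraph sets the control rate at 50%, names no other, and refers to this study. The caption of Figure 3 speaks of 200 donors per year, which over two years of recruitment is the same 400.

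A second point is that only the 79% contradicts Table 1 on its face, while the 95% is a smaller miss that shows up only on recalculation. That is true as to size. Still, Table 1 determines the curve, and 95% at 70% does not lie on it.

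Third, this is an exploratory pilot, both figures understate power, and Table 1 is correct. All of this stands. The article also says that the trial's findings, not these planning figures, will inform the later trial. These points limit the consequences but do not make the two sentences right.

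**Conclusion.** The point holds. At 67%, the stated 79% is impossible beside the 90% given for 65.9%, at any alpha. On the inputs that generate Table 1, power is 93.5% at 67% and 98.5% at 70%. Across the usual variants of the test the ranges are 91.9% to 93.9% and 98.0% to 98.6%.

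The exact sizes rest on a two-sided alpha of 0.05, inferred from Table 1, and on equal arms of 200. The contradiction at 67% needs neither assumption. Since both errors understate power, the planned sample size is not called into question for these scenarios. Even 300 donors would give about 85% power at 67%.

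**What to change.** Restate the two sentences from the paragraph's own inputs: with 400 donors, 1:1 allocation, a 50% control rate and a two-sided alpha of 0.05, power is 93% if the intervention rate is 67% and 98% if it is 70%. State the alpha and sidedness there, because the reader now has to infer them from the table.

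If 79% and 95% were computed from other inputs, give those inputs and say why they differ from Table 1. If the two power values are to be kept under the present inputs, attach them to the rates they belong to, 63.7% and 67.6%.

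In each case, check Figure 3 against the same formula and inputs. The cost is two sentences and one figure check, with no change to sample size, analysis or conduct.

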**Figure 3 figure3:**
[figure not shown]
Power calculation of piloting mKidney with 200 donors per year.

### Analysis

Research team members at Johns Hopkins will conduct all analyses for this pilot RCT. Descriptive statistical methods will be used to analyze the frequency of key variables, including chi-square and rank-sum tests. Rates of the follow-up compliance among participants in the intervention and control arms will be compared using generalized linear regression. We will perform subgroup analyses for younger donors (age at donation<40 years), older donors (age ≥40 years), men, and women. In addition, the impact of the mKidney system on LKD follow-up compliance will be compared with historical follow-up with a difference-in-difference framework. All analyses will follow an intention-to-treat principle. Data will be analyzed with Stata 15 for Linux (StataCorp Inc).

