### Inclusion and Exclusion Criteria

For the pilot RCT, LKDs who have donated a kidney at the Methodist Specialty and Transplant Hospital during the study period will be eligible for study participation. We will exclude LKDs who do not speak English or own a smartphone device; by national policy, all donors are ≥18 years of age.

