The primary outcome of interest will be the rate of policy-defined complete (all components addressed) and timely (60 days before or after the expected visit date) submission of data at all 6-month, 1-year, and 2-year follow-up visits, compared between study arms. The secondary outcome will be the transplant hospital-level compliance with OPTN reporting requirements at each visit. Outcomes will be assessed independently for each follow-up time point and as a composite outcome over the study period, as well as will be compared between study arms following the intention-to-treat principle. To understand logistical or demographic barriers to implementation, we will also collect process data and utilize routinely collected data on LKDs in the study. These data include age, sex, race, ethnicity, and educational level of LKDs.

There will not be study-specific efforts to retain participants or promote the use of the mKidney app for LKD follow-up data submission, as this would be a form of intervention that might impact outcomes. However, transplant providers at Methodist Specialty and Transplant Hospital may contact LKDs for obtaining complete and timely LKD follow-up data to comply with nationally mandated follow-up requirements. Participants may withdraw from the RCT at any time without penalty. Withdrawal from the RCT would not preclude participants from obtaining regular medical care or follow-up care related to their kidney donation. If participants choose to withdraw, the study team will use the data collected prior to withdrawal and mark the remaining data as censored. Other than interventions that might impact the rates of LKD follow-up compliance, no concomitant care or interventions will be prohibited during the trial.

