#### Special Populations

LKDs at Methodist Specialty and Transplant Hospital have historically been predominantly Caucasian and Hispanic; thus, recruitment of African Americans and Asian LKDs might be limited. We will consider age-related issues to technology adaptation and use, which could be a limitation to the implementation of the mKidney system. Based on recent trends at our pilot site, we anticipate approaching patients with a wide distribution of age.

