#### Need for Tailoring for Differences in Adoption Among Different Racial and Ethnic Groups

Should we receive feedback that differs based on factors, such as sex, age, race or ethnicity, and health literacy, it might be necessary to tailor the mKidney system or design a different mHealth system to mitigate the potential for health disparities. The UNOS Living Donor Committee has expertise in the design, development, and cultural tailoring of transplant education materials and tools should the need arise to develop different versions.

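### Effect of mKidney by age is planned only as a split at 40, which is inefficient for a gradual age trend; add an exploratory arm-by-age term with age continuous

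*Protocol article*

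**What the plan says.** All places are in the protocol article; no separate analysis plan is shown.

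- Analysis: "We will perform subgroup analyses for younger donors (age at donation<40 years), older donors (age ≥40 years), men, and women". No reason is given for the cut at 40, and no analysis with age on its own scale is stated. The main comparison is described thus: "Rates of the follow-up compliance among participants in the intervention and control arms will be compared using generalized linear regression".
- Special Populations: "We will consider age-related issues to technology adaptation and use, which could be a limitation to the implementation of the mKidney system", followed by "Based on recent trends at our pilot site, we anticipate approaching patients with a wide distribution of age".
- Inclusion and Exclusion Criteria: "by national policy, all donors are ≥18 years of age". No upper limit is stated.
- Study Procedure: process data and routine donor data will be used to understand barriers to implementation, and "These data include age, sex, race, ethnicity, and educational level of LKDs". Age is therefore held for every participant.
- Study Design and Objective: the trial is an exploratory pilot, meant to supply effect sizes for a larger multicenter trial.

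**The concern.** The article expects a wide age range and names age as a possible obstacle to use of the app, yet it looks at the effect by age through two averages. The older group runs from 40 to the oldest donor. If benefit declines with age, the decline among the oldest is averaged with donors in their 40s, and the variation in age inside each group is not used.

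What is at stake is the design of the later trial, for which the shape of the effect across age is a direct input. The primary result of this pilot is not affected.

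**Working it through.** **Inputs.** From the article: 400 donors, 1:1 allocation, control compliance 50%, minimum age 18. Assumed, because the article does not give them: two-sided alpha 0.05 and the age distribution.

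**1. The plan's own figure.** The article gives no power figure for the age groups, so the overall one is reproduced. For 200 per arm with pooled variance under the null:

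power = Φ{[d − 1.96√(2p̄(1−p̄)/n)] / √[(p₁(1−p₁)+p₂(1−p₂))/n]}

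- 50% against 63.8%: 79.8% (stated 80%).
- 50% against 65.9%: 89.9% (stated 90%).

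The 400-donor row of Table 1 is confirmed.

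**2. Information lost by the split.** For an effect linear in age, the share kept is the squared correlation between age and the indicator of age 40 or over. With a proportion q under 40:

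- Normal age: share kept = φ(z_q)² / [q(1−q)]. At q = 0.5, 0.3989²/0.25 = 0.637, a loss of 36.3%, the smallest possible. At q = 0.4 the loss is 37.8%; at q = 0.3 it is 42.4%.
- Normal age truncated to 18–75, mean 38 to 46, SD 10 to 14: loss 33% to 44%.
- Flat age: share kept = 3q(1−q). For 20–60, q = 0.5 and the loss is 1 − 0.75 = 25%. For 18–70, q = 22/52 = 0.423 and the loss is 27%.

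**3. What the split can detect.** With 40% under 40 there are 80 per arm in the younger group and 120 per arm in the older. For effects of 25 and 5 points:

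variance = 0.25/80 + 0.75×0.25/80 + 0.25/120 + 0.55×0.45/120 = 0.00961, so SE = 0.098.

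For 80% power the two groups' effects must differ by (1.96 + 0.84) × 0.098 = 0.275. Other splits between 35% and 50% under 40 give about 27 to 28 points.

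**4. Simulated power for the arm-by-age term.** 400 donors, age normal with mean 42 and SD 12 truncated to 18–75, control rate 50%, linear probability model with robust SE, 3,000 trials per scenario:

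| True effect by age | Split at 40 | Continuous (linear) |
|---|---|---|
| Same at all ages (type I error) | about 5% | about 5–6% |
| Linear fall, 12 points per 12 years | 46% | 65% |
| Linear fall, 1.2 points per year | 61% | 81% |
| 25 points to age 45, falling to 0 at 65 | 11% | 23% |
| +20 points below 55, −10 from 55 | 13% | 29% |
| +20 points below 60, none from 60 | 6% | 9% |
| Step at 40: 29 points below, 3 from 40 | 77% | 57% |

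Repeat runs gave 44–47% against 63–67% for the 12-point linear fall, 11–13% against 23–25% for the late decline, and 6% against 9–10% for no effect from 60. For the 12-point linear fall, a 3-knot spline reached 54%, between the split (44% in that run) and the linear term (63%).

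**5. How the groups would look.** In the late-decline case the two age rows would show 25 and about 17 to 18 points, while donors aged 60 or over gain about 2. With mean 38 to 46 and SD 11 to 12, 47% to 68% of the older group are in their 40s, and about 9 to 46 of the 400 are 60 or over. Even with 46 (23 per arm), the SE of an arm difference near 50% is √(2×0.25/23) = 0.147, a 95% interval of about ±29 points.

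**The case against.** Several objections have force.

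- **The size of the loss is not fixed by the documents.** A reader might infer that the split throws away over a third of the age information. That holds for normal ages; flat ages give 25% to 27%, and the article's expectation of a wide age range does not exclude them. This stands.
- **The split is not always worse.** If the effect truly changes at 40, the split wins (77% against 57%). This stands. Nothing in the article points to a step there, and keeping the two rows covers that case.
- **Continuous age does not rescue the oldest group.** A reader might infer that it would reveal an app that does nothing for donors aged 60 or over. At 9% to 10% power it would not. Nor would the split plainly show equal benefit in the late-decline case, since 25 against 17 to 18 points shows the direction.
- **Age-related use is examined elsewhere.** The Abstract and Study Procedure plan process data on implementation, and Participant and Data Confidentiality gives the analysts the app's raw data and audit logs. These show use by age more directly than an interaction on compliance. So the split is the only stated look at the *effect* by age, not the only use of age.
- **Ethnicity and education.** The article raises tailoring ("Should we receive feedback that differs based on factors, such as sex, age, race or ethnicity, and health literacy") and collects ethnicity and education without listing them as subgroups, so a reader might infer a second fault. A condensed article may leave further subgroups to the full plan, and the text does not say who gives the feedback. That inference is not supported.
- **This is an exploratory pilot and the subgroups are secondary.** True, and it limits the weight of the point. It does not remove it, because the split is what the article itself specifies and a better method is available at almost no cost.

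**Conclusion.** The point holds in a limited form. The stated analysis of effect by age is inefficient for a gradual trend, losing about 25% to 44% of the age information (about 36% or more if ages are normal). Under the assumed ages, continuous age raises power for a linear fall of 12 points per 12 years from about 46% to 65%, and for a late decline from about 11% to 23%, with type I error near 5% for both. These figures rest on an assumed age distribution, a 50% control rate and two-sided 0.05.

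The gain is in estimating an age trend for the later trial. Power for any age interaction stays modest, and a failure confined to donors aged 60 or over would probably be missed under either analysis.

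**What to change.** In the Analysis section, add an arm-by-age term to the planned generalized linear regression with age at donation continuous: linear as the main form, since it has more power than a spline for a steady trend, and a 3-knot spline as a sensitivity check. Report the arm difference with its confidence interval at several ages, labelled exploratory. Keep the under-40 and 40-and-over rows as a display, which also covers a step near 40. Specify this before outcomes are analysed by arm.

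The cost is a few lines of analysis on data already collected. The downside is a few more exploratory estimates with wide intervals, especially at the oldest ages, and the report should say so.
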